The target trial for the influenza vaccine is very similar, but differs slightly due to the seasonality of the disease. Influenza viruses are constantly mutating, necessitating yearly changes of the influenza vaccines. It is therefore recommended to estimate influenza vaccine effectiveness on a seasonal basis instead (30). The target trial is therefore also defined on a seasonal basis, meaning that there is one target trial per influenza season that should be emulated. Recruitment would start each year on the first of September. People may then be recruited and followed up until the end of May of the next year (31.05.).

Both target trials are pragmatic, in the sense that no placebo control is used. We choose to formulate them this way because it is generally impossible to emulate placebo-controlled randomized controlled trials using only observational data (27). We further assume perfect adherence, so that every individual randomized to the treatment group actually receives the respective vaccination strategy and every individual in the control group does not. Our main interest is therefore in the *per-protocol* effect, although we will also estimate *intention-to-treat* effects in a sensitivity analysis, as described in detail in Section 2.6.3. Because we compare the vaccine effectiveness of patients with autoimmune diseases and other patients, but are unable to randomize the disease status itself, we are interested mainly in the *effect modification* of the disease status on the vaccine effectiveness (31). The result is a comparison of two population-based total causal treatment effects (32).

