#### 2.6.1 Matching method

Due to the different target trials per vaccine of interest, the planned matching and analysis strategy also differs slightly. To analyze the effectiveness of the herpes zoster vaccine, a single matching process will be used. For the influenza vaccine effectiveness trials we will use the same procedure, with the only difference being that it will be performed separately for each influenza season. The matching will be carried out as follows.

For the previously defined start date of the respective trial, the eligibility of all individuals contained in the BARMER database will be determined using the above mentioned inclusion criteria. Eligibility will be checked using only the information available at that time. Every individual who was vaccinated with the vaccine of interest on this date is subsequently included in the dataset, in the treatment group. For every individual included in this way, we then include *k* further individuals who fulfill the inclusion criteria, but have not been vaccinated yet, in the control group. These controls will be matched exactly by age in years, gender, place of residence and disease group. If more than *k* potential controls are identified for a case, *k* controls will be picked at random from these. We will try to include 2 controls per case first (*k* = 2), but will lower this number to 1 if the number of available matches is insufficient. The date of inclusion equals “time zero” (27) for all individuals. Information about all relevant confounders is recorded as available on this date, corresponding to baseline information. This procedure is repeated on all subsequent days, until the emulated trial is over.

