#### 2.6.2 Analysis method

The matching process described above reduces the time-dependent vaccination variable to a time-fixed binary variable, allowing the use of well known analysis methods. We will first describe the matched data using descriptive statistics, stratified by treatment group and disease status. Means and standard deviations will be calculated for normally distributed continuous variables, median and ranges will be used for non-normally distributed continuous variables and counts and percentages will be calculated for categorical and binary variables. Appropriate statistical tests, such as *t*-tests and chi-squared tests, will be used to formally compare the distribution of these variables at baseline. Histograms and boxplots, stratified by both treatment groups and disease groups will also be drawn. In addition, the number of vaccinated individuals, matched controls and number of potential controls evolving over time will be graphically displayed as recommended by Thomas et al. (56).

For the estimation of the vaccine-effectiveness, we will employ standard time-to-event analysis methods, such as Kaplan-Meier curves and Cox models. No complex marginal structural models or similar strategies are required, because only information before inclusion into the trial is used for adjustment, making it impossible for *treatment-confounder* feedback (32) to occur.

Because we only match by age in years, gender, place of residence and disease status, we still have to adjust for the other confounders mentioned earlier to obtain unbiased estimates of the average causal effect we are interested in. A Cox model using the time to the respective outcome of interest as dependent variable and the treatment variable, the disease status and all relevant confounders (as observed at trial inclusion) as independent variables will be used to perform this adjustment. Since we are interested in the effect-modification of the vaccine effectiveness by disease status, we will also include an interaction term of these two variables in the model. This model, in conjunction with an estimate of the baseline hazard function (60), will then also be used to estimate confounder-adjusted survival curves using g-computation (61). These curves will then be used to derive time-dependent relative risk estimates, which will in turn be used to derive the vaccine effectiveness as (62):

(1)
$$\begin{array}{l} \theta \left(t\right)=1-RR\left(t\right), \end{array}$$

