by disease status, where *t* denotes the point in time and *RR*(*t*) is the relative risk of experiencing the respective outcome at time *t* in the vaccinated vs. unvaccinated group. Formal contrasts of the disease specific vaccine effectiveness estimates will then also be calculated. Cluster-robust standard errors will be used in the Cox model to adjust for potential dependencies introduced by matching (63). Non-parametric bootstrapping will be used to derive confidence intervals for the vaccine effectiveness and their formal comparisons. Although Abadie and Imbens (64) demonstrated analytically that bootstrapping is not a valid strategy to estimate standard errors in matched samples, it has been shown to work well in simulation studies (65). Due to these simulation results and a lack of alternatives we will therefore still rely on this method.

A very similar analysis strategy will be used to assess the moderating effect of the prior use of immunosuppressive medication on the vaccine effectiveness. In this analysis, only individuals with MS, IBD, or CIRD will be included. The entire analysis described above is then repeated, stratified by disease group and the severity of the received immunosuppresive medication (if any). Additionally, g-computation will be used to estimate the age-specific vaccine-effectiveness in each trial. To obtain a single estimate for the influenza vaccine, we will also use standard meta-analytic approaches to combine the estimates obtained from each of the four emulated influenza trials.

The proportional hazards assumption will be checked using Schoenfeld residual plots (66). If the assumption is deemed violated, we will try different strategies, such as inclusion of time-dependent hazard-ratios and variable transformations, to alleviate this issue. If these methods are unsuccessful, other models such as the additive hazards model (67) with a similar specification will be employed instead. In addition, we will perform a sensitivity analysis in which we will use a weighted Kaplan-Meier estimator instead of g-computation (68), where the weights will be estimated using entropy balancing (69).

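### Age-specific vaccine effectiveness is planned from a Cox model whose only stated vaccine interaction is with disease status, so as written it carries almost no information about age

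*Protocol article*

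**What the plan says.** Section 2.6.2 (Analysis method) describes the Cox model by its terms: "the treatment variable, the disease status and all relevant confounders (as observed at trial inclusion) as independent variables will be used to perform this adjustment". Because effect modification by disease is of interest, it adds one interaction, between vaccination and disease status: "we will also include an interaction term of these two variables in the model". The same model, with an estimate of the baseline hazard, supplies the g-computation survival curves. On those curves the section says: "These curves will then be used to derive time-dependent relative risk estimates". VE is one minus the relative risk, by disease status.

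The age-specific analysis is a single sentence later in the section: "Additionally, g-computation will be used to estimate the age-specific vaccine-effectiveness in each trial". No other model is attached to it. Table 1 describes the same Cox model and g-computation and adds no age-varying vaccine effect. The only analysis described as stratified is the one on immunosuppressive medication.

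**The concern.** G-computation averages predictions from a fitted model and cannot recover a pattern that the model rules out. If the vaccine effect may differ by disease status but not by age, each age in a disease group receives the same estimated hazard ratio. The resulting VE by age would then be close to that group's overall VE repeated at each age, whatever the data show.

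At stake is the meaning of one planned result. A near-flat series of age-specific estimates could be read as evidence that the vaccine works equally well at all ages, when the model assumed it. The authors include a vaccine-by-disease term because they want modification by disease. The same reasoning calls for a vaccine-by-age term when VE by age is wanted.

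**Working it through.** The article states no VE by age, event risk or age distribution, so there is no figure of its own to reproduce. The check asks what the stated model can return.

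**1. Closed form.** Let *r* be the unvaccinated risk at time *t* for a given age, and HR the hazard ratio for that disease group. Under proportional hazards without a vaccine-by-age term, the vaccinated risk is 1 − (1 − r)^HR, so

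VE(t | age) = 1 − [1 − (1 − r)^HR] / r.

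Age enters only through *r*. The values of HR and *r* below are assumptions spanning a range.

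| HR | r = 0.1% | 1% | 5% | 10% | 20% |
|---|---|---|---|---|---|
| 0.30 | 69.99% | 69.89% | 69.46% | 68.89% | 67.62% |
| 0.50 | 49.99% | 49.87% | 49.36% | 48.68% | 47.21% |
| 0.60 | 39.99% | 39.88% | 39.39% | 38.74% | 37.34% |

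For HR 0.60 the values at risks of 0.2% and 4% are 39.98% and 39.51%. In all three rows VE moves by less than one percentage point while the risk is at most 5%. That drift comes from baseline risk, not from any estimated difference in vaccine effect by age.

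**2. Simulation.** Assumptions, none from the article: 60,000 vaccinated, half of them diseased, matched 1:1 on age group and disease; true HR 0.3 in younger and 0.6 in older people, identical with and without disease; 30% older among the diseased and 70% among the non-diseased; yearly hazard 0.03 (younger) and 0.06 (older), multiplied by 1.5 if diseased; one year of follow-up. A Cox model with a Breslow baseline was fitted and VE taken by g-computation.

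| VE, younger / older | Model as stated | With vaccine-by-age term | True (hazard-ratio scale) |
|---|---|---|---|
| Non-diseased | 44.1% / 43.7% | 67.5% / 38.7% | 70% / 40% |
| Diseased | 55.6% / 54.8% | 68.3% / 40.0% | 70% / 40% |
| Pooled over disease | 53.2% / 48.2% | 68.1% / 39.2% | 70% / 40% |

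On the relative-risk scale the true values are almost the same. For the non-diseased, 1 − (1 − e^−0.009)/(1 − e^−0.03) = 69.7% and 1 − (1 − e^−0.036)/(1 − e^−0.06) = 39.3%.

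The pooled row has a five-point gradient even though the model contains no age modification. It arises because the younger stratum holds more diseased people, to whom this model assigns a higher VE.

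**3. The disease contrast under the same assumptions.** The true risk ratio among each group's own vaccinated follows directly.
- Non-diseased: unvaccinated risk 0.3 × 0.02955 + 0.7 × 0.05824 = 0.0496; vaccinated risk 0.3 × 0.00896 + 0.7 × 0.03536 = 0.0274; VE 44.7%.
- Diseased: unvaccinated risk 0.7 × 0.04400 + 0.3 × 0.08607 = 0.0566; vaccinated risk 0.7 × 0.01341 + 0.3 × 0.05257 = 0.0252; VE 55.6%.
- Ratio 55.6 / 44.7 = 1.24.

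The simulated fits gave 1.26 both with and without the vaccine-by-age term. So the stated model recovers the contrast over each group's own age mix, and the missing term does not alter it. Standardised to one common age mix, the ratio was 1.26 without the term and 1.02 with it.

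**The case against.** **The article does not exclude an age interaction.** It explains the one interaction it names and gives one sentence to age-specific VE, and a fuller plan may hold the detail. This stands in part: nothing forbids the term. But the article does more than leave a gap. It writes out the model, derives the curves from it, and announces an output that this model cannot deliver.

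**Age-specific VE is peripheral.** It appears neither in the aims (Section 2.1) nor among the causal contrasts of Table 1. This stands and limits the severity.

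**The planned checks may protect the analysis.** Section 2.6.2 has Schoenfeld plots, time-dependent hazard ratios, an additive hazards fallback, and a weighted Kaplan–Meier sensitivity analysis planned regardless of the check. Together these largely cover variation of the effect over time, so a reader should not infer that the time-dependent relative risk is unprotected. They do not cover age: the check and its remedies concern time, and the weighted Kaplan–Meier analysis is not described as being by age.

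**A reader might infer that the primary disease contrast is biased by age.** Matching is within disease group ("These controls will be matched exactly by age in years, gender, place of residence and disease group"), so it does not align ages between diseased and non-diseased. If VE varies with age and the age mixes differ, the ratio can depart from 1 with no effect of disease at any given age. The documents do not support calling this an error. Table 1 fixes the effect on the treated as the estimand, and Section 2.2 describes the aim in these words: "The result is a comparison of two population-based total causal treatment effects (32". Averaging each group over its own vaccinated members is that comparison.

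**Conclusion.** The point holds for the age-specific analysis only. If the Section 2.6.2 model is used as written, VE within a disease group is constant across age on the hazard-ratio scale. On the relative-risk scale it is nearly constant for rare outcomes: about 1.2 percentage points between risks of 0.2% and 10% at HR 0.60 (39.98% − 38.74%). If the estimates are pooled over disease groups, any gradient reflects baseline risk and disease mix and does not measure age modification.

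The near-constancy follows from the model's form and needs only that outcome risks are not high. How misleading the result would be depends on how much VE truly varies with age, which the article does not give; the 70%/40% example is an illustration.

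Severity is minor to moderate: the stated aims and the Table 1 contrasts are unaffected.

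**What to change.** For the age-specific analysis, state that the outcome model includes a flexible vaccine-by-age term (spline or age bands), with vaccine-by-age-by-disease where the data allow. Alternatively, fit the model by age band before g-computation. Say also whether age-specific VE will be reported within disease groups or pooled over them.

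The cost is a few model terms and wider age-specific intervals, especially in MS and IBD.

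Optionally, report as a supplementary result the disease contrast standardised to a common age distribution, using the model with the age term, and note that the primary contrast compares populations with their own age mixes. This takes one further averaging step. It aids interpretation and does not correct the primary estimand.

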#### 2.6.3 Intercurrent events

Four possible types of events that may happen to individuals after inclusion into the study need to be accounted for. These possibly events are:

Death.Loss to follow-up.Individuals receiving another unplanned vaccination after the first dose (e.g., non-adherence to the “assigned” treatment status).Individuals *not* receiving a planned second vaccination (only applicable to the herpes zoster vaccine effectiveness study).

Of course, death may occur at any time for any number of reasons, while loss to follow-up may only occur when individuals terminate their enrollment in the BARMER health insurance company. The third type of intercurrent event requires more considerations. In practice, individuals may receive another vaccination after already having received the recommended amount of doses. Additionally, because only information at the time of inclusion is used when performing the matching, it is possible that individuals which were selected as controls get vaccinated themselves during follow-up. Lastly, because the matching is performed on the date of first vaccination, it is possible that individuals do not receive a planned second vaccination as recommenced for herpes zoster vaccines.

In all analyses, individuals will be considered right-censored at their time of loss to follow-up or death (whichever occurs first). In the primary *per-protocol* analysis, the event time of individuals will also be censored at the time at which they receive a vaccination that does not correspond to the planned treatment strategy, or at the time at which they should have received a second vaccination but did not do so. This way, only time during which the individuals adhered to their assigned treatment is considered in the analysis. This strategy likely results in covariate-dependent censoring, which will be accounted for by also censoring the matched pair of the individual at the same time (56). In the secondary *intention-to-treat* analysis, the subsequent vaccinations are ignored instead, which results in all potential effects of non-adherence to the assigned treatment to be included in the analysis.

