Treatment Assignment	Individual randomization, stratified on disease status (MS, IBD, CIRD or none of these).	To emulate randomization we adjust for multiple confounders using a combination of matching and g-computation.
Start and end of trial	(1) Herpes zoster vaccine effectiveness trial: 01.12.2018–31.12.2021^a^ (2) Influenza vaccine effectiveness trials:*^b^* (a) 01.09.2015–31.05.2016 (b) 01.09.2016–31.05.2017 (c) 01.09.2017–31.05.2018 (d) 01.09.2018–31.05.2019	
Start and end of follow-up	Start of follow-up: time of assignment to treatment strategy. End of follow-up: The earliest of death, loss-to-follow-up or administrative end-of-follow-up (end of the respective study).	
Outcomes	(1) Herpes zoster vaccine effectiveness: medically attended Herpes zoster infection (2) Influenza vaccine effectiveness: (a) medically attended influenza infection (b) severe medically attended influenza infection	
Causal contrast	(1) The ratio between the vaccine effectiveness (1 - the relative risk to develop the outcome at time *t* given the treatment) in the diseased group (individual has either MS, IBD or CIRD) and the non-diseased group (2) The vaccine effectiveness for each of the three disease groups (MS, IBD, CIRD), stratified by the categorized severity of received medication in regards to immunosuppressive effect. Both contrasts will be estimated as *intention-to-treat* and *per-protocol* effects. The target estimand is the average causal effect on the treated (ATT).	
Statistical analysis	Computing formal contrasts of simple Kaplan-Meier estimates.	Time-dependent 1:1 matching by days without replacement. Controls will be matched exactly by age in years, biological sex, place of residence, and disease status. The matched sample will be analyzed using a Cox model with additional adjustment for further confounders. G-computation based on this Cox model and a non-parametric estimate of the baseline hazard will be used to estimate the target estimand. Both *intention-to-treat* and *per-protocol* effects will be estimated by different censoring schemes as described in Section 2.6.3.
Sensitivity analysis	None.	The entire analysis will be repeated using *medically attended urinary tract infection* as a negative control outcome to assess the robustness of the confounder adjustment employed.

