**Vaccination plan**	
For individuals with MS, IBD, or CIRD it is not unusual that the vaccination is planned in advance by the physician and aligned with changes in medication that may have immunosuppressive effects. For example, the physician may decide that the individual should be vaccinated next week. To allow the patients immune system to make a proper response to the vaccination, a new prescription of immunosuppressive medication is then delayed for a few weeks. This variable states whether such a plan was made or not.	An indicator of whether a person receives a medication change shortly after vaccination may be created. However, this type of indicator breaks the time-line, since information from the future would be used. We will perform an additional sensitivity analysis to determine the effect of using this indicator as an adjustment variable.

Using this DAG and the *backdoor criterion* (47), we then identified separate sets of factors that we need to adjust for in each vaccine effectiveness analysis (53). These sufficient adjustment sets are very similar. In both of the two considered analyses, we will adjust for *Age, Sex, Place, Calender Time, Cautiousness, Disease Status, Healthcare-Seeking Behavior* (HSB), *Treatment, Health Status*, and *Vaccination Plan*. The only differences are that we additionally have to adjust for *Chicken Pox* and *Herpes Zoster Immunity* in the herpes zoster vaccine effectiveness analysis and that we also have to adjust for *Influenza Immunity* in the influenza vaccine effectiveness analysis.

Note that, given our assumptions, there is no need to adjust for socioeconomic status in either analysis, because we hypothesize that the effect of this variable on each outcome is only indirect and is thus already adjusted for by including the other variables. It is also not strictly necessary to adjust for sex in the influenza vaccine effectiveness analysis for the same reason. We choose to include sex anyway, because it can be seen as a proxy for other relevant confounders such as cautiousness that we may not be able to fully adjust for given the mentioned indicators (48).

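### Primary per-protocol analysis: censoring the matched partner corrects only for the matching variables, leaves post-baseline and unmeasured drivers of crossover uncorrected, and is undefined for two controls per vaccinee

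*Protocol article*

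**What the plan says.** Section 2.2 sets the priority: "Our main interest is therefore in the *per-protocol* effect, although we will also estimate *intention-to-treat* effects in a sensitivity analysis". Section 2.6.3 calls the per-protocol analysis primary and has event times "censored at the time at which they receive a vaccination that does not correspond to the planned treatment strategy". The same applies to zoster vaccinees at the point where a second dose was due but not given.

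For the resulting dependence, Section 2.6.3 offers one remedy: "This strategy likely results in covariate-dependent censoring, which will be accounted for by also censoring the matched pair of the individual at the same time". No censoring weights are named.

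On what partners have in common, Section 2.6.1 says: "These controls will be matched exactly by age in years, gender, place of residence and disease group". The inclusion date is shared as well. All other measured confounders enter a Cox model at their values at inclusion (Section 2.6.2). The same section states: "No complex marginal structural models or similar strategies are required, because only information before inclusion into the trial is used for adjustment".

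Table 2 (Vaccination plan) notes that in MS, IBD and CIRD it can happen that "the vaccination is planned in advance by the physician and aligned with changes in medication that may have immunosuppressive effects". Section 2.5.4 says the nodes of the causal graph vary over time, and that no valid indicator was found for cautiousness.

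On the matching ratio, Table 1 reads "Time-dependent 1:1 matching by days without replacement", while Section 2.6.1 reads "We will try to include 2 controls per case first" and falls back to one control if matches are too few.

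**The concern.** A control who is vaccinated leaves the risk set at that moment. If something that also affects infection risk prompted the vaccination, the remaining controls are selected on it. Removing the partner equalises follow-up time within the pair. It removes a comparable vaccinee only to the extent that the partner shares the factor, and beyond the matching variables the partner need not share it. Treatment, health status, healthcare-seeking and cautiousness are all in the protocol's adjustment set and are not matched.

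The justification in Section 2.6.2 is that adjustment uses only information from before inclusion. That is sound for baseline adjustment and for the intention-to-treat effect. Per-protocol censoring is triggered by what happens after inclusion, so the argument does not cover the primary effect.

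At stake is the primary estimate of vaccine effectiveness (VE) in each disease group. Separately, with two controls per vaccinee, the protocol does not say who is censored when one control crosses over.

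**Working it through.** **Inputs.** From the protocol: the per-protocol priority, the censoring rule, the matching variables, baseline-only covariates and the two matching ratios. It gives no control uptake, event rate or censoring fraction, so there is no stated figure to reproduce. Every numerical input below is assumed. In these simulations only controls deviate.

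**Step 1: which drivers does each device handle?** Setup: 100,000 matched sets, 4 replicates, conditional hazard ratio 0.5, and three binary factors, each multiplying the outcome hazard by e^1.1 ≈ 3.0. M is matched. L is unmatched but in the Cox model. U is in neither. Control vaccination hazard is 0.3, or 0.3 × e^1.8 ≈ 1.8 when the driver is present. Uptake over the unit of follow-up is then 1 − e^(−0.3) ≈ 26% or 1 − e^(−1.8) ≈ 83%. This is a deliberate stress test. VE = 1 − RR at the end of follow-up; the target without deviation is about 0.41.

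| Driver of crossover (1:1) | Kaplan-Meier, own censoring only | Kaplan-Meier, partner censored | Cox/g-computation, own only | Cox/g-computation, partner censored |
|---|---|---|---|---|
| M (matched) | 0.33 | 0.43 | 0.42 | 0.42 |
| L (measured at baseline) | 0.33 | 0.33 | 0.42 | 0.42 |
| U (neither) | 0.33 | 0.33 | 0.34 | 0.35 |

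The partner rule repairs selection through M. For L the Cox model does the repair, not the partner rule. For U neither does. A factor arising after baseline is likewise neither matched nor in the model.

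**Step 2: size for a post-baseline driver.** Assumed: 6 million pairs, a factor arising in 20%, 90-day uptake rising from 25% to 55% when it is present, outcome hazard multiplied by 2 or 3, and 29% of controls censored. VE = 1 − HR.

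| | HR, true 1.00 (×2 / ×3) | HR, true 0.60 (×2 / ×3) | VE, true 40% |
|---|---|---|---|
| Partner censoring | 1.043 / 1.075 | 0.629 / 0.648 | 37.1% / 35.2% |
| Own censoring only | 1.039 / 1.074 | 0.628 / 0.647 | 37.2% / 35.3% |
| Censoring weights, factor known and dated | 0.998 / 1.001 | 0.603 / 0.603 | 39.7% / 39.7% |

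The bias is 40 − 37.1 = 2.9 to 40 − 35.2 = 4.8 points. A second run of this scenario gave partner-censored HRs of 0.62 / 0.64, that is VE 38% / 36%. If the factor lowers uptake, VE is overstated by 1 to 2 points.

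**Step 3: range over uptake.** Same structure, true VE 40%, with onset of the factor and length of follow-up (up to 270 days) varied.

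| 90-day uptake without / with factor | Estimated VE |
|---|---|
| 25% / 55% | about 35–39% |
| 10% / 25% | 38–39% |
| 5% / 15% (about 6–7% of controls censored) | 39–40% |
| 2% / 5% | about 40% |

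**Step 4: two controls per vaccinee.** If the whole set is censored at the first crossover and a fraction q of controls cross over independently, 1 − (1 − q)² of sets are censored. At q = 0.30 this is 1 − 0.70² = 51%, against 30% with one control. In the Step 1 setup with driver M, three readings of the rule give these Kaplan-Meier results:

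- whole set censored at the first crossover: 0.44
- vaccinee censored at the last control's crossover: 0.40
- vaccinee censored at the first crossover, other control kept: 0.50

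Cox/g-computation gives about 0.42 under all three with driver M, and 0.34 to 0.36 with driver U.

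**The case against.** The strongest reply is that the planned devices together cover a good deal. Partner censoring handles the matched variables. The Cox model handles treatment severity, healthcare-seeking, comorbidity, level of care and vaccination history as measured at baseline. Step 1 confirms both, and this stands. A reader might infer that the partner rule achieves nothing; the check does not support that.

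The size is also open. Section 2.6.1 expects only a relatively small share of people to be vaccinated, and at low uptake the bias is about 1 point or less. This stands too, although uptake in strata matched to vaccinees may exceed the average.

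Cross-checks are planned, but they do not close the gap:

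- The intention-to-treat analysis has no artificial censoring, but a difference from per-protocol mixes selection with dilution by crossover.
- The negative control outcome repeats the analysis, so it may flag bias but cannot remove it.
- The vaccination-plan sensitivity analysis adds an adjustment variable; it is not a model of when controls cross over.
- The weighted Kaplan-Meier sensitivity analysis names entropy-balancing weights and does not mention censoring.

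Weighting has limits as well. The near-exact recovery in Step 2 assumes a factor that is perfectly measured and dated. Section 2.5.3 says outpatient diagnoses may be placed only within an interval of up to 91 days, and no weight can use unmeasured cautiousness.

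Finally, a set-level rule could be left to the analysis plan, and the fallback to one control makes the pair rule well defined. The contradiction between Table 1 and Section 2.6.1 remains either way.

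**Conclusion.** The point holds in a limited form. In the primary per-protocol analysis, selection through the matching variables and through measured baseline covariates is addressed, provided the Cox model is correct. Selection through post-baseline or unmeasured drivers is not, so the protocol should not claim that covariate-dependent censoring has been dealt with.

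For a post-baseline driver and a true VE of 40%, the bias under assumed inputs runs from under 1 to about 5 points. Its sign depends on whether the driver raises or lowers uptake. The larger gap for U in Step 1 (0.41 against 0.35) comes from a stress test and shows the pattern, not an expected size.

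A reader might go on to infer that the bias carries into the comparison of diseased with non-diseased people, because Table 2 describes planned vaccination timing for the disease groups. That is possible, but it was not computed and the protocol gives no figures for it. Nor do the documents show that the primary method must be replaced outright.

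The conflict over the matching ratio, and the lack of a censoring rule for a set of three, follow from the text and need no simulation.

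**What to change.** 1. Pre-specify a second per-protocol analysis that censors only the person who deviates and applies truncated inverse-probability-of-censoring weights. Use baseline covariates plus time-updated covariates that carry exact dates: prescriptions, admissions, and contacts where dated.
2. Report it beside the pair-censored estimate, and state that unmeasured drivers such as cautiousness remain uncorrected in both.
3. In Section 2.6.3, say that partner censoring addresses the matching variables only. In Section 2.6.2, limit the statement on marginal structural methods to baseline adjustment and the intention-to-treat effect.
4. Make Table 1 and Section 2.6.1 give the same matching ratio. If two controls are kept, replace the pair wording with a set-level rule under which one control's crossover censors neither the vaccinee nor the remaining control.

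The cost is some wording, one censoring model per emulated trial, and some added variance from the weights. Part of that variance is recovered because vaccinated follow-up is no longer discarded when a control crosses over.
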